## Methods

### NMES protocol

To assess spinal motor control network excitability, we will apply NMES on the extensor carpi radialis (ECR) and/or flexor carpi radialis (FCR) during the HMI movement task. The applied NMES will trigger H-reflex in the muscle and resultant MEP will be captured using the Trigno Avanti EMG sensors with two sensors placed on the ECR and two on the FCR muscles. The location of the ECR is found by using a motor map derive from a cursor pixel/EMG relationship as shown in Figure 2. Similarly, the muscle belly is identified by having the subject place their forearm down on a flat surface with their palm down, then extending their wrist towards the thumb and back. The FCR is found by using the motor map, and/or having the subject place their forearm on a flat surface with their palm up to identify the muscle belly. To do so, the subject brings their thumb to their middle finger and flexes their wrist so their fingers point to their elbow. While the subject is in the flexed position the contracted muscle belly is found by touching the muscle. The NMES will be applied over two channels (one for ECR and one for FCR) and will be produced using a Hasomed RehaStim in Sciencemode controlled via Labview (settings—Baudrate: 115200; Data Bits: 8; Parity: None; Stop Bits: 2; Flow Control: CTS). Labview triggers the stimulation when the cursor begins entering the target area. Stimulation levels are determined using a ramp up, initially, with a 5 mA amplitude 250 μs pulse, and then incremented by 5 mA until reaching the individuals maximum comfort range. For repeated NMES, we use an amplitude that is 85% of that maximum (although some may require higher for a more profound effect). To verify the NMES triggered MEP, the stimulation should evoke a contraction that is at least 25–30% of a maximum voluntary contraction (54) as measured using the HMI which minimizes the likelihood of a startling effect.

### TMS protocol

TMS (MAG & More) will be used to probe the neuromuscular controller at the cortical level using a series of motor evoked potentials (MEP). The MEP will perturb the neuromuscular movement using the HMI to affect a feed-forward external modification to brain-level issued motor commands, and to act as a disturbance in motor learning.

The anatomical landmarks for TMS localization will be identified using 3-Tesla functional magnetic resonance imaging (fMRI) of the wrist primary motor cortex area (M1). To do so, all subjects will undergo wrist activation experiments during fMRI consisting of three 30-s periods of rest alternating with three 30-s periods of wrist extension and flexion at a rate of approximately 0.5 Hz (55). Brainsight neuro-navigation will be then be used with the generated fMRI mappings to localize the wrist ECR and FCR target hotspots. High field strength at the localized wrist extensor and flexor hotspots will be verified by measuring 10 consecutive TMS-evoked peak-to-peak MEPs with an average amplitude of 0.5-1 mV at a rate of approximately 0.5 Hz (56). More than 10 consecutive MEPs can be used, but here, we implement 10 since this amount provides a high reliability (57, 58). Although TMS exhibits some variability, the MEP amplitude inconsistencies that are expected over time do not affect this protocol’s ability to assess corticospinal behavior.

Finally, it is worthwhile to note that TMS and NMES are not required to be used simultaneously, as the motor response can be measured in succession as described below. They can be used either in subsequent movements or following a > 60 ms voluntary stimulus evoked delay window (59).

### tDCS protocol

When considering the HMI movement task, we will also apply anodal tDCS to modulate motor control excitability to determine how movements are scaled (60). To perform the task under tDCS we apply similar methods to those presented in earlier studies, such as by Lackmy-Vallee et al. (61). Specifically, we will use a 10/20 EEG guided placement verified by our TMS to determine anode placement. We will apply a 2 mA current which corresponds to the mean intensity threshold ascertained in a study that examined the functional architecture of the motor homunculus for tDCS (62), and similar to the intensity used in other studies (63). Anodal stimulation will be applied for 15 min prior to performing the movement task with the HMI. The anode will be placed over M1 (targeting wrist extensor or flexor) while the cathode is placed over the contralateral supraorbital area. Here, we apply tDCS prior to the motion but it has been shown to be effective when administered before the task as well. Thus, precise tDCS stimulus/perturbation timing during the task is not required.

We also apply sham stimulation for control purposes by placing electrodes on the same positions and stimulating for 120 s at the start and 30 s at the end. The sham stimulation is applied with a 2 mA current based on previously accepted methods (61–63).

The tDCS will be introduced into the protocol after TMS as the mechanism as it (anodal tDCS) entails depolarizing the neurons to increase the probability of action potential—TMS is used first to induce an action potential. Research has also shown that certain neurons that are inactive respond strongly to the TMS. tDCS will be used in an online fashion where anodal stimulation will be provided during the task.

Electrode sizes of 5 cm × 7 cm are used.

### The blended NIBS-NMES method

Our blended neurostimulation protocol combines the aforementioned tools into a single combined protocol aimed at isolating cortico-spinal neuromuscular control pathways and to measure the distinct pathway features related to neurorehabilitation intervention.

During a volitional motor task, the application of TMS generates a feedforward perturbation onto the motor control dynamics. Specifically, the resultant MEP change is thus measured by a change in contraction amplitude, a change in the phasic activity in burst contractions, as well as in the co-ordination effect on a multi-muscle system (ECR vs. FCR). The effect of the generated TMS perturbed and volitional MEPs is modulated by tDCS such that motor excitability increases to affect the feedforward mechanisms of the motor controller. In this way our combined TMS + tDCS protocol provides an impulse-response probing tool to identify unique person-specific feedforward motor behavior (64). Where, impulse-response dynamics are ubiquitous for their use in understanding wide-band frequency behaviors of complex time-invariant systems. Thus, the TMS generated impulse creates a neurological mapping of kinematic-EMG dependencies based on the cortically generated motor control plan. Whilst, tDCS neuromodulation of the M1 provides system modification (through motor excitability) that would be captured in a subsequent impulse-response measurement. As a result, this gives us a tool to identify the causal relationships between brain-muscle pathways, and more importantly, how they change over time during motor learning (65, 66) (see Figure 3). Data acquisition and stimulation are controlled with a single computer, time-synced system, and thus all data are time stamped to ensure synchronization.

**Figure 3 fig3:**
[figure not shown]
NMES impulse pathway. NMES typically first triggers the sensory-afferent pathway, then affects the homonymous efferent pathway to generate a MEP. The spinal-muscle section in this mode is shared with the feedforward TMS triggered pathway, but does not share the descending brain-spinal cord network elicited through TMS.

Additionally, the NMES impulse at the spinal-level creates a secondary measurable dynamic response. NMES applied at the muscular level triggers direct motor response (M wave) and/or a closed-loop afferent-spino-muscular response (NMES ➔ muscle) that captures the neural dynamics related to the motion (also see Appendix) (38). For example, M1 issued motor commands are a feed-forward representation of the movement strategy, thus by perturbing only the spinal-level motor controller the cortical feed-forward mechanisms remain intact, but spinal-level computations are altered. It is important to note that although the afferent-to-efferent pathway shown in Figure 3 includes the sensory-motor feedback loop in the motor controller, the NMES triggers short latency neuromuscular stimulation in a feedforward matter (i.e., direct path from NMES to muscle stimulation) and thus does not represent a closed loop mechanism. The true feedback response comes after the initial NMES stimulation (M wave), following spinal or cortical level processing (H-reflex or F wave). Additional information on the behavior of these mechanisms can also be found in our earlier computational studies of the corticospinal system (4, 67–69). The NMES thus provides impulse-response dynamics of short-latency sensory-modified motor control strategies irrespective of cortical driven movement formation (70).

In terms of the system response, the dynamic control motor outputs, MO, of these pathways are defined using standard representative systems:

(1)
$$MO_{TMS}=M\left(s\right)CP\left(s\right)R_{TMS}\left(s\right)$$

(2)
$$MO_{NMES}=M\left(s\right)SP\left(s\right)R_{NMES}\left(s\right)$$

Where, R is the input function. Individually these system representations denote their unique stimulation-response pathways, e.g., cortico-muscular or spinal-muscular, CP is the cortical pathway, SP is the spinal pathway, as shown in Figures 3, 4. If both pathways are known through application of TMS and NMES, their relative contributions can be discovered mathematically such that:

(3)
$$\begin{array}{c} MO_{TMS}-MO_{NMES}=\Delta_{MC}=M\left(s\right)CP\left(s\right)R_{TMS}\left(s\right)\\ -M\left(s\right)SP\left(s\right)R_{NMES}\left(s\right) \end{array}$$

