Thus Equation 7 shows that the spinal-level isolated impulse-response, SP(s), can be measured by comparing the response characteristics due to TMS and NMES. Similarly, Equation 9 shows that the cortical-level isolated impulse-response, CP(s), can also be measured in a similar way. However, what is important to identify as part of these equations that the muscle pathway motoneuron effect, M(s), is removed. This reduces controller block sizes, and separates the cortical and spinal functionality before motor execution. In other words, the unshared portions of the neural impulse-responses can be investigated [CP(s): brain to spinal cord pathway; and SP(s): afferent sensory pathway]. This is novel in that the complexity of delineating cortical and spinal systems is exceptionally difficult due to their shared endpoint networks. Based on our earlier studies, these computational representations of the complex non-linear motor controller have been validated with similar NIBS based studies measuring motor response times (4, 67–69). Specifically, although a linear approach is taken above, the components of the system are highly non-linear and have shown a robust ability to emulate the corticospinal motor controller.

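### Equation 2 has no term for the direct M-wave response that the article says NMES can evoke, so the SP(s) from Equation 7 is not purely spinal whenever an M wave is present

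*Protocol article*

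**What the plan says.** The text leading to Equations 1 and 2 (Protocol article, Methods, The blended NIBS-NMES method) describes two possible responses to NMES: "NMES applied at the muscular level triggers direct motor response (M wave) and/or a closed-loop afferent-spino-muscular response". It adds that "the NMES triggers short latency neuromuscular stimulation in a feedforward matter (i.e., direct path from NMES to muscle stimulation"), and it puts the two in order: "The true feedback response comes after the initial NMES stimulation (M wave), following spinal or cortical level processing (H-reflex or F wave").

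Equation 2 then gives the NMES motor output as the product of three terms: the shared motoneuron-muscle block M(s), the spinal pathway SP(s) and the input R_NMES(s). No term in Equations 1–9 stands for a direct stimulator-to-muscle response.

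After Equation 9 the article says that "the spinal-level isolated impulse-response, SP(s), can be measured by comparing the response characteristics due to TMS and NMES", and that "the unshared portions of the neural impulse-responses can be investigated [CP(s): brain to spinal cord pathway; and SP(s): afferent sensory pathway"].

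The NMES protocol section says "The applied NMES will trigger H-reflex in the muscle and resultant MEP will be captured" by the EMG sensors on the ECR and FCR. The stated check is on force: "To verify the NMES triggered MEP, the stimulation should evoke a contraction that is at least" 25–30% of a maximum voluntary contraction, read from the HMI.

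**The concern.** By the article's own account, the NMES response may contain a part that reaches the muscle directly, before any spinal processing. SP(s) is defined as the afferent sensory pathway and presented as isolated, yet the equation it is solved from has nowhere else to put the direct part. Unless MO_NMES is restricted to the later reflex response, the direct part is counted as spinal.

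SP(s) is one of the two quantities that the method is meant to deliver. The contrast CP(s)−SP(s) carries the stated expectation for stroke patients, who are to be measured at three or more points in their rehabilitation (Expected outcomes). A direct component would distort the level of both quantities. If it drifted between sessions, the drift could be read as a change in spinal function.

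**Working it through.** **Inputs.** Equations 1–9, the definition of SP(s), and the statement that NMES may evoke an M wave all come from the blended NIBS-NMES section. The article gives no figure for the size of the M wave, so there is no stated figure to reproduce.

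**Step 1: the equations as printed.** With a common normalised input R:
- MO_TMS = M·CP·R and MO_NMES = M·SP·R.
- Δ_MC = MO_TMS − MO_NMES.
- Equation 7: (MO_TMS − Δ_MC)/(M·R) = MO_NMES/(M·R) = SP.
- Equation 9: (MO_NMES + Δ_MC)/(M·R) = MO_TMS/(M·R) = CP.

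The algebra is consistent. However, the subtraction in Equation 7 only gives back the NMES response divided by M·R. The comparison with TMS removes nothing from it.

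**Step 2: add the direct path.** Let D be the direct (M-wave) path, so that MO_NMES = R·(M·SP + D). Then:
- Equation 7 returns SP + D/M.
- Equation 5 returns M·(CP − SP) − D.
- Equation 9 still returns CP.

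A numerical check at random complex values of M, CP, SP, R and D agrees with all three results, with errors below 1e-15.

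**Step 3: size, under an assumption.** Let f = D/(M·SP + D) be the direct share of the NMES output. Then D/M = SP·f/(1−f), and the estimate of SP is SP/(1−f). The last column takes CP = 1 and SP = 0.5 for illustration (true difference 0.5) and equals 1 − 0.5/(1−f).

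| Assumed f | SP multiplied by | CP−SP read as |
|---|---|---|
| 0.10 | 1.11 | 0.44 |
| 0.25 | 1.33 | 0.33 |
| 0.50 | 2.00 | 0.00 |
| 0.75 | 4.00 | −1.00 |
| 0.90 | 10.00 | −4.00 |

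**Step 4: change over time.**
- *Absolute change.* Between two sessions, the change in Equation 5 is the true change in M·(CP−SP) minus (D2 − D1). If D is constant it cancels. If D varies, the difference passes straight through. In the illustration, with CP and SP unchanged, a fall in f from 0.50 to 0.25 moves the reading of CP−SP from 0.00 to 0.33, which is the direction the article expects from learning.
- *Relative change in SP.* With D/M constant, a true relative change δ is read as δ·(1−f), where f is the share at the first session. A true 30% change reads as 0.30 × 0.75 = 22.5% at f = 0.25, and 0.30 × 0.50 = 15% at f = 0.50.

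**Step 5: does any text restrict MO_NMES to the reflex?**
- The Figure 2 caption mentions a delayed secondary peak and links the equations to the offset between stimulation and cursor movement. The cursor is driven by force, and the caption gives no rule for separating components.
- The window of more than 60 ms in the TMS protocol section concerns the use of TMS with NMES, not the M wave against the H-reflex.
- Study limitations makes only a general caveat about separability and does not mention the M wave.
- The NMES check is on total evoked contraction, which an M wave alone could satisfy.

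**The case against.** The strongest reply is that the authors know the two components and separate them in time. They place the feedback response after the M wave, they record EMG with synchronised time stamps, and the Figure 2 caption points to a delayed secondary response. MO_NMES may therefore be meant as the reflex part alone. The Appendix cited at that sentence and Figure 3 are not at hand, and Study limitations calls the equations simplified. This shows that the intention may be sound and the correction easy. It does not supply the missing definition, and Equation 2 as printed still disagrees with the text just before it. An omitted path is also not covered by a caveat about non-linearity, since it biases SP even in a linear system.

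A reader might infer several stronger things that the documents do not support:
- *That SP would mostly reflect direct muscle excitation.* No M-wave share is given, and the article's and/or wording allows little or no M wave.
- *That the planned comparison over time is invalid.* A constant D cancels from the absolute change in CP−SP, which is the form of the stated expectation. The article does not name relative change in SP as its measure.
- *That SP is computed from force.* No text says so. The contraction criterion is a check on the stimulus that also bears on startle. What stands is that it cannot by itself show that an H-reflex was evoked.
- *That the article contradicts itself on closed-loop behaviour.* The wording is loose, but the text explains that the early response is feedforward and the feedback comes later.

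**Conclusion.** The point holds as a mismatch between a stated equation and the stated physiology. With a direct component D, Equation 7 returns SP + D/M and Equation 5 is shifted by −D, while CP from Equation 9 is unaffected. The level of SP and of CP−SP is therefore biased whenever an M wave is included in MO_NMES. Absolute change over time is biased only if the direct component (strictly D/M, once M is divided out) differs between sessions, for example through electrode position or stimulation amplitude. Any relative change in SP is diluted by the factor 1−f.

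The algebra is exact given an additive direct path. The size is not known: inflation of 1.33 times at f = 25% and 2 times at f = 50% rests wholly on assumed shares, and the bias is nil where no M wave is evoked or where MO_NMES is in fact limited to the reflex.

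**What to change.** 1. Define MO_NMES in Equations 2–9 as the EMG response in a latency window after the M wave, with the window stated in advance. Alternatively, add an explicit direct term D(s) to Equation 2 and state how it is estimated and removed before SP is computed.
2. Confirm the H-reflex for each participant on the EMG sensors already placed on the ECR and FCR, in addition to the contraction check.
3. Where no reflex is detectable, report SP, and any contrast that uses it, as not estimable.

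Normalising the H-reflex to the M wave is not needed. It would replace the impulse response with a different quantity.

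The cost is a revised definition and one extra reading of data already being recorded. The downside is that SP will be missing for some participants, which should be reported alongside the results.

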**Figure 4 fig4:**
[figure not shown]
TMS impulse pathway. TMS triggers the feedforward network to generate a MEP. The impulse-response characteristic relates TMS-EEG and is driven primarily by the feedforward/efferent pathway (red).

Such that the change in motor command dynamics, ∆*
_MC_
*, is defined by:

(4)
$$\Delta_{MC}=M\left(s\right)\left[CP\left(s\right)R_{TMS}\left(s\right)-SP\left(s\right)R_{NMES}\left(s\right)\right]$$

Or, given that the input is a normalized function:

(5)
ΔMCR(s)=M(s)[CP(s)−SP(s)]

In other words, the measured difference in the change in motor response is proportional to the difference in motor control input from cortical, CP(s), and spinal-level, SP(s), commands. This represents an important concept to delineate hierarchical control paradigms. Specifically, the blended neurostimulation protocol enables the shared neuromuscular controller to be probed in such a way to identify unique cortical- and spinal-level contributions to the motor control strategy.

Similarly, if 
$\Delta_{MC}/R\left(s\right)\;$
measures the motor level activity, we can infer unique CP or SP contributions to the motor control outcome as well. For example, by taking Equations 1–5:

(6)
MOTMSR(s)−ΔMCR(s)=M(s)CP(s)−M(s)[CP(s)−SP(s)]

(7)
$$\frac{MO_{TMS}-\Delta_{MC}}{M\left(s\right)R\left(s\right)}=SP\left(s\right)$$

And, by taking Equations 2 and 5:

(8)
MONMESR(s)+ΔMCR(s)=M(s)SP(s)+M(s)[CP(s)−SP(s)]

(9)
$$\frac{MO_{NMES}+\Delta_{MC}}{M\left(s\right)R\left(s\right)}=CP\left(s\right)$$

Thus Equation 7 shows that the spinal-level isolated impulse-response, SP(s), can be measured by comparing the response characteristics due to TMS and NMES. Similarly, Equation 9 shows that the cortical-level isolated impulse-response, CP(s), can also be measured in a similar way. However, what is important to identify as part of these equations that the muscle pathway motoneuron effect, M(s), is removed. This reduces controller block sizes, and separates the cortical and spinal functionality before motor execution. In other words, the unshared portions of the neural impulse-responses can be investigated [CP(s): brain to spinal cord pathway; and SP(s): afferent sensory pathway]. This is novel in that the complexity of delineating cortical and spinal systems is exceptionally difficult due to their shared endpoint networks. Based on our earlier studies, these computational representations of the complex non-linear motor controller have been validated with similar NIBS based studies measuring motor response times (4, 67–69). Specifically, although a linear approach is taken above, the components of the system are highly non-linear and have shown a robust ability to emulate the corticospinal motor controller.

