Later, we will apply this new method as part of a clinical-based study to explore motor re-learning for neurorehabilitation. Patients participating in the study will undergo this protocol in at least three milestones of their neurorehabilitation protocol: (a) Immediately following stroke, at the start of the treatment; (b) at an approximate half-way point during their rehabilitation plan; and (c) at the end of the neurorehabilitation plan (either in a clinical or at-home setting). We will use the blended neurostimulation protocol to measure changes to the neuromuscular controller from baseline, and track their progress over time. By measuring impulse-response dynamics of the corticospinal system, we will identify how these control pathways change—specifically, how they issue motor commands during re-learning—over time. We expect, much like with healthy subjects, there will be an increase in the feedforward pathway such that CP(s)—SP(s) (see Equation 5) becomes more positive. We also expect to see that the peak MEP variability associated with TMS impulse decrease over time as reported in earlier studies. Inter-test repeatability is inconsistent across NIBS studies, but it has been shown that the variability decreases with repeated stimulation and/or neuromodulation (not necessarily the peak amplitude of the MEP) (76). This coincides with what we expect in motor learning, since as the feedforward controller improves, less internal variation will occur in the issued motor command and subsequently less emphasis given to sensory-driven command formulation.

Ultimately, this new method gives clinicians and scientists a unique template to understand variable across populations, changes in individuals over time based on motor learning, and allows healthy and diseased states to be classified cross-sectionally.

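### Equations 7 and 9 only rearrange Equations 2 and 1 and still divide by M(s), so comparing TMS with NMES does not isolate SP(s) or CP(s) as the protocol states

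*Protocol article*

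**What the plan says.** The section on the blended NIBS-NMES method models each motor output as a product of a shared block M(s), a pathway block and an input. Equation 1 is MO_TMS = M·CP·R_TMS and Equation 2 is MO_NMES = M·SP·R_NMES. Equation 3 defines Delta_MC as the first output minus the second. Equation 5 takes a common input R, "given that the input is a normalized function", which gives Delta_MC/R = M(CP − SP). Equations 6 to 9 lead to two results:

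- Equation 7: SP = (MO_TMS − Delta_MC)/(M·R)
- Equation 9: CP = (MO_NMES + Delta_MC)/(M·R)

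The text then concludes: "Thus Equation 7 shows that the spinal-level isolated impulse-response, SP(s), can be measured by comparing the response characteristics due to TMS and NMES". It says the same of Equation 9 and CP(s), and adds that "the muscle pathway motoneuron effect, M(s), is removed".

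Expected outcomes builds the stroke hypothesis on this model. Over rehabilitation, with at least three assessments, the expectation is that "CP(s)—SP(s) (see Equation 5) becomes more positive".

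**The concern.** Telling cortical from spinal contributions apart is the stated purpose of the protocol, and these equations are offered as the means. Delta_MC is not a third measurement: it is computed from the same two outputs. If it drops out on substitution, the comparison of TMS with NMES contributes nothing to either isolated response. If M(s) still has to be known, the statement that it has gone is contradicted by the equations just above it.

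The cost falls on the longitudinal readout. Nothing in the text shown holds M(s) constant across training or recovery, so a change in the shared block could be reported as a change in the balance of cortical and spinal control. The comparison of healthy with diseased states in Expected outcomes is exposed in the same way to differences in M(s) between people.

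**Working it through.** **Inputs.** Equations 1, 2, 3, 5, 7 and 9 as listed above, with a common R as Equation 5 assumes.

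**Step 1: reproduce the protocol's result.** Equations 7 and 9 do follow from Equations 1 to 5. As algebra they are valid.

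**Step 2: substitute Equation 3.**

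- Equation 7 numerator: MO_TMS − (MO_TMS − MO_NMES) = MO_NMES, so SP = MO_NMES/(M·R). This is Equation 2 rearranged, and the TMS response has cancelled.
- Equation 9 numerator: MO_NMES + (MO_TMS − MO_NMES) = MO_TMS, so CP = MO_TMS/(M·R). This is Equation 1 rearranged, and the NMES response has cancelled.

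A numerical check with random complex values gave the same identities.

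**Step 3: count what is identified.** There are three unknowns (M, CP, SP) and two outputs. The system has rank 2, and it stays at 2 when Delta_MC is added. Replacing M by kM, CP by CP/k and SP by SP/k leaves both outputs unchanged. At k = 0.5, 2 and 4, SP and CP change by factors of 2, 0.5 and 0.25 with identical data. Only CP/SP is unaffected.

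**Step 4: see what Equation 5 observes.** The values here are illustrative and do not come from the protocol. Set R = 1 and hold CP = 1.2 and SP = 1.0, so that CP − SP = 0.20 throughout.

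| M | MO_TMS = 1.2M | MO_NMES = 1.0M | Delta_MC/R | MO_TMS/MO_NMES |
|---|---|---|---|---|
| 1 | 1.2 | 1.0 | 0.20 | 1.20 |
| 1.5 | 1.8 | 1.5 | 0.30 | 1.20 |
| 2 | 2.4 | 2.0 | 0.40 | 1.20 |

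The difference moves in proportion to M although neither pathway has changed. The last row (2.4 and 2.0) would also arise from M = 1, CP = 2.4 and SP = 2.0, and the data cannot tell the two cases apart. The direction is not fixed either. If CP = 1.0 and SP = 1.2, the same rise in M gives −0.20, −0.30 and −0.40.

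**Step 5: find what survives.** Dividing Equation 1 by Equation 2 gives MO_TMS/MO_NMES = (CP/SP)·(R_TMS/R_NMES). M cancels if it is the same block under both stimuli. The input ratio does not cancel. For a response magnitude within one person, the change in log(MO_TMS/MO_NMES) equals the change in log(CP/SP) plus the change in log(R_TMS/R_NMES).

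The common input matters for Equation 7 as well. Take M = 1.3, CP = 2.0, SP = 0.7, R_TMS = 1 and R_NMES = 0.5, again only as an illustration. Then MO_TMS = 2.6, MO_NMES = 0.455 and Delta_MC = 2.145. Equation 7 with R = R_TMS returns (2.6 − 2.145)/1.3 = 0.35 for a true SP of 0.70.

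**The case against.** **M(s) may be obtained elsewhere.** A reader might infer that the protocol has no way to measure M(s). The documents do not support that. The article refers to an Appendix and to earlier computational studies, none of which is shown, and an estimate could be there. What stands is that the text shown gives none.

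**Removed may mean divided out.** On that reading the right-hand sides are free of M(s) and there is no algebraic error. That is fair, but dividing by M(s) requires knowing it, and the text goes on to claim that both responses can be measured.

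**Equation 5 is described correctly.** The text says "the measured difference in the change in motor response is proportional to the difference in motor control input" and prints M(s) as the factor. That wording is not a fault. The difficulty arises only when Expected outcomes reads change over time in CP − SP without saying that M(s) is constant.

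**Latencies behave differently.** The Figure 2 caption ties Equations 1 to 9 to the delay between stimulation and cursor movement. Delays of serial blocks add, so a shared delay would cancel in a latency difference. This is a real point for a latency readout, but Equations 7 and 9 subtract outputs, not latencies.

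**Limits are already conceded.** Study limitations admits linear simplification and incomplete separation, and presents the work as a first step. It mentions neither M(s) nor the redundancy of Delta_MC, and the problem is present even if the linear model is exactly true.

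**The M wave might stand in for M(s).** A reader might infer that normalising to the M wave settles the matter. The article describes M(s) as a motoneuron effect, which a direct muscle response need not capture, and it describes NMES as producing the M wave and/or the reflex response. The M wave is therefore not a ready substitute.

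**Conclusion.** The point holds. Within the protocol's own model, Equations 7 and 9 add nothing to Equations 2 and 1, M(s) is not removed, and the two outputs do not identify SP(s), CP(s) or CP − SP without further information on M(s). This is a positive statement contradicted by adjacent equations, not a detail left to another document.

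The conclusion on the algebra needs no assumption beyond Equations 1 to 3 and the common R. The consequence for the longitudinal readout depends on M(s) changing between assessments. The documents give no figure for that, so the size and direction of any distortion are unknown. The rise from 0.20 to 0.40 in the working reflects only the chosen doubling of M and should not be read as an estimate of bias.

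Nor should a reader infer that the TMS and NMES comparison is worthless. It supports a statement about relative contributions, an aim the article also names, provided M(s) is shared by both stimuli and the input ratio is known or constant.

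**What to change.** 1. Withdraw the statements after Equation 9 that M(s) is removed and that Equations 7 and 9 isolate SP(s) and CP(s).
2. Base the longitudinal readout, and the hypothesis in Expected outcomes, on the within-person change in log(MO_TMS/MO_NMES) for the same muscle and movement direction.
3. State the conditions with it: M(s) is shared by both stimuli; R_TMS/R_NMES is known or held constant across sessions; and the direct M wave is separated from the NMES reflex response, since only the latter passes through SP(s).
4. Report separate CP and SP values, or CP − SP, only where an independent estimate of M(s) is described or constancy of M(s) is stated as an explicit assumption. If the Appendix contains such an estimate, cite it at Equations 7 and 9.

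**Cost.** Mainly rewriting the derivation and the hypothesis, plus documenting the inputs at each session. Whether the planned EMG already separates the M wave from the reflex is not established in the text shown, so some change to recording or processing may be needed. The claim weakens from isolated CP(s) and SP(s) to their relative change, and a change that scales both pathways equally will not be seen.
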